### Primary outcome measures

The primary outcome measure is memory retrieval function assessed by delayed recall of Auditory Verbal Learning Test-Huashan version (AVLT-H). To be specific, participants were asked to study a list of 12 frequent and concrete words three times. Words were presented acoustically and free recall was measured in an immediate recall condition, a 5-min short delayed recall condition, and a 20-min long delayed recall condition.

### Secondary outcome measures

Secondary outcome measures include neuronal plasticity metrics obtained by MRI. Structural MRI using three-dimensional (3D)-T1 and diffusion tensor imaging (DTI) techniques will be adopted to investigate gray matter volume, white matter fiber integrity, and nerve fiber connectivity among cognition-related brain regions (prefrontal lobe and parietal lobe) and memory-related brain regions (hippocampus, medial temporal lobe, and prefrontal lobe) in participants before and after cognitive control training. Functional MRI (fMRI) will be used to reveal changes in the cerebral activation. Resting-fMRI and task-fMRI will be performed to statistically compare changes in regional function signals within episodic memory- and cognitive control-related brain regions (frontal, prefrontal, and parietal lobes), and changes in connectivity among implementation, memory and default networks, especially the prefrontal lobe-hippocampus function connection. For task-fMRI, a scan with an episodic memory task will be included.

### Data collection

Demographic data (gender, age, educational level, and occupation), medical and disease histories, and results of physical examinations, nervous system examinations, neuropsychological evaluations, and blood analyses are collected from consecutive patients according to exclusion criteria. Qualified individuals will receive structural and functional head MRI scans.

Routine blood tests will be performed for detection of blood cell counts, liver and kidney function, blood glucose levels, thyroid function, folic acid and vitamin b12 levels, and syphilis and HIV antibodies.

After 12 weeks of cognitive training, repeat physical examinations, nervous system examinations, neuropsychological evaluations, and structural and functional MRI will be performed (Fig. 1).

### Neuropsychological assessment

The neuropsychological assessment employs several commonly used measures of cognitive and daily functions. Measures include MMSE, MoCA, CDR, AVLT-H, Boston Naming Test (BNT), DIGIT span test (DST), TRAIL Making Test (TMT), Hachinski Ischemia Scale (HIS), Geriatric Depression Scale (GDS), and ADL assessment. Of these, CDR, HIS, GDS, and ADL will only be performed in the recruitment phase (Fig. 2). Furthermore, in the memory domain, episodic memory tasks that include a learning session and a test session will be conducted both outside and inside the scanner.

**Fig. 2 Fig2:**
[figure not shown]
Standard Protocol Items: Recommendations for Interventional Trials (SPIRIT) figure with the schedule of enrollment, interventions and assessments. MRI magnetic resonance imaging, MMSE Mini-mental State Examination, MoCA Montreal Cognitive Assessment, BNT Boston Naming Test, AVLT-H Auditory Verbal Learning Test - Huashan version, DST DIGIT span test, TMT TRAIL Making Test, CDR Clinical Dementia Rating, HIS Hachinski Ischemia Scale, GDS Geriatric Depression Scale, ADL Activities of Daily Living

### MRI protocol

All participants will receive MRI scans at baseline and after 12 weeks of cognitive training using an identical 3-T device (GE DISCOVERY MR750) in the same scan modes. The 3D-T1 structural images of the brain will be obtained by 3D magnetization-prepared rapid acquisition with gradient echo (3D-MPRAGE) using the following acquisition parameters: 176 sagittal slices; thickness = 1 mm; TR = 8.2 ms; TE = 3.2 ms; flip angle = 8°; FOV = 250 × 250 mm; and matrix = 256 × 256. fMRI scan will be performed using a T2-weighted echo-planar imaging (EPI) sequence with the following acquisition parameters: slices = 43; TR = 2000 ms; TE = 30 ms; flip angle = 90°; FOV = 220 × 200 mm; and matrix = 64 × 64. DTI will be conducted using a single excitation EPI sequence and the following scan parameters: FOV = 192 × 192 mm; TR = 8600 ms; TE = 84 ms; b = 1000 s/mm^2^; diffusion sensitive gradient magnetic fields = 30; slices = 67; thickness = 1.5 mm; layer interval = 0 mm; NEX = 2; and 4 b0 images. Image quality will be validated by an experienced imaging specialist. Individuals with potential cerebral impairments or structural abnormalities revealed by neuroimaging will be excluded from subsequent experiments.

### Data monitoring

All neuropsychological evaluations will be conducted by the same neuropsychologist, all MRI scans completed using an identical machine, and image quality examined after each scan cycle.

### Sample size estimates

According to a previous study [41], in which computerized cognitive training was administered for six weeks, the mean difference in AVLT-H score between the cognitive training and control groups was 0.26 ± 0.3. Based upon this difference, 22 samples are required to yield a statistical power of 80% at a statistical significance level of 0.05. The sample size was estimated using the following equation:$$ n=\frac{\left({q_1}^{-1}+{q_2}^{-1}\right){\left({t}_{\alpha /2}+{t}_{\beta}\right)}^2{S}^2}{\delta^2} $$

where q_1_ and q_2_ are the sample size ratio of two groups (q_1_ = q_2_ = 0.5), α is the statistical significance level (α = 0.05), β is calculated from 1-β which stands for statistical power (1-β = 0.8), δ is the mean difference (δ = 0.26), and S is the standard deviation (S = 0.3) used in the analyses. Considering the instability of standard deviation and dropout rate, the sample size for each group is set as 35.

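### The power statement rests on an AVLT-H standard deviation of 0.3, unit and sub-score unstated, which is not credible for a single recall count out of 12 words

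*Protocol article*

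**What the plan says.** Primary outcome measures (protocol article): "The primary outcome measure is memory retrieval function assessed by delayed recall of Auditory Verbal Learning Test-Huashan version (AVLT-H"). On administration, "participants were asked to study a list of 12 frequent and concrete words three times", with free recall tested immediately, after 5 minutes and after 20 minutes. The article does not say which delayed condition, or what combination of the two, is the primary score.

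Sample size estimates: the input comes from a cited six-week computerised training study, where "the mean difference in AVLT-H score between the cognitive training and control groups was 0.26 ± 0.3". The text then fixes the terms of its equation: "δ is the mean difference (δ = 0.26") and "S is the standard deviation (S = 0.3) used in the analyses". The result is that "22 samples are required to yield a statistical power of 80% at a statistical significance level of 0.05". The number per group is raised to 35 to allow for an unstable SD and for dropout, but neither an alternative SD nor a dropout rate is given.

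Statistical analysis: group-by-time ANOVA on each dependent variable. With two time points, the interaction is a comparison of mean change between arms.

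Discussion: dropout was built into the sample size so that the study would have adequate power.

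**The concern.** The inputs imply a standardised effect of 0.26/0.3 = 0.87. That ratio bears on the primary endpoint only if 0.26 and 0.3 are a mean difference and a between-patient SD on that endpoint's scale. The endpoint, as described, is a count of words recalled from a list of 12. Patients' counts, or their changes in count, would hardly ever differ from one another if their SD were 0.3 words.

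This calculation is the only justification given for 70 patients. If 0.26 is a difference in words and the SD is anywhere near a whole word, the trial has little power for 0.26. A null result could then be read as evidence of no effect from an adequately powered trial.

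**Working it through.** **Inputs.** From Sample size estimates: δ = 0.26, S = 0.3, two-sided α = 0.05 (the equation uses α/2), power 80%, q₁ = q₂ = 0.5, final n = 35 per group. From Primary outcome measures: a 12-word list. Assumed, because the article gives no figure: 20% dropout (28 per arm) and SDs of 0.5 to 2 words.

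**1. The plan's own figure.** The equation gives the total:

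n = (1/q₁ + 1/q₂)(t_{α/2} + t_β)² S²/δ²

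- With normal quantiles: 4 × (1.960 + 0.842)² × 0.09/0.0676 = 41.8 in total, or 21 per arm.
- Iterated with t quantiles: 43.8 in total, or 22 per arm.
- Exact noncentral-t power at 22 per arm: 80.2%. If 22 were the total (11 per arm), power would be 49%.

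So 22 is the per-group number and it is correct on the stated inputs. At 35 per arm the same inputs give 94.7%.

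**2. What an SD of 0.3 means for a word count.** If a proportion q of patients lies off the commonest whole-number score, the variance is at least q(1 − q). Setting q(1 − q) = 0.3² = 0.09 gives q = 0.10. At least 90% of an arm must share one score, with the rest one word away. The same holds for change in a single count, which is also a whole number. If the raw SD were 2 words (assumed), a change-score SD of 0.3 would need a baseline-to-outcome correlation of 1 − 0.09/(2 × 4) = 0.989.

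**3. The whole-number bound.** A whole-number score has variance of at least f(1 − f), where f is the fractional part of its mean. With arm means 0.26 apart, the smallest possible pooled SD is 0.310 and the smallest possible SD common to both arms is 0.336.

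**4. How far the increase to 35 reaches.** Solving exact t power = 80% for the SD, with δ = 0.26:

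- 35 per arm: SD up to 0.383.
- 28 per arm: SD up to 0.341.

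Even at SD 0.383, q(1 − q) = 0.147 gives q = 0.18, so about 82% of an arm would need the same score.

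**5. Power for δ = 0.26 words over a range of SDs (exact t, two-sided 0.05).**

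| SD (words) | 35 per arm | 28 per arm |
|---|---|---|
| 0.3 (as stated) | 95% | 89% |
| 0.5 (assumed) | 57% | 48% |
| 1.0 (assumed) | 19% | 16% |
| 1.5 (assumed) | 11% | 10% |
| 2.0 (assumed) | 8% | 8% |

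**6. Other readings of 0.26 ± 0.3.**

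- Both in one linearly rescaled unit: d = 0.87 is unchanged and power at 35 per arm is about 95%, but 0.26 is then not a number of words.
- 0.26 is itself a standardised effect (SD 1): power at 35 per arm is 19%.
- 0.3 is the standard error of the difference: z = 0.26/0.3 = 0.87, p about 0.39 in the source, and the SD is unknown.

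**7. What 35 per arm can detect.** Solving for the difference at 80% power: 0.68 SD at 35 per arm, 0.76 SD at 28.

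**The case against.** Four objections carry weight.

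First, a reader might infer from the bounds in step 3 that an SD of 0.3 is impossible. It is not. S is given to one decimal, and 0.310 and 0.336 both round to 0.3. At those SDs, power at 35 per arm is still 93% and 89%. If the primary score averaged the 5-minute and 20-minute recalls, it would move in half-word steps and the bounds would drop to 0.177 and 0.214. The article states no averaging but does not exclude it. The bound shows implausibility and does not by itself defeat the power claim.

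Second, a reader might infer that the trial is shown to be underpowered. The article gives no SD for AVLT-H in this population, so every power figure below 80% in step 5 rests on an assumed SD. On the common-rescaling reading the standardised effect and its power survive, and the fault is then only an unstated unit.

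Third, the source of 0.26 ± 0.3 is not at hand, so the unit, the sub-score and the SD-or-SE question cannot be settled here.

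Fourth, the plan did allow for SD uncertainty by going from 22 to 35 per group, a 59% increase. That is true, but the same increase must also cover dropout, and it stretches the tolerable SD only from 0.30 to 0.383.

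What remains is that, on the endpoint as described, 0.3 is not a credible between-patient SD, and the article gives nothing that would let a reader accept it on another scale.

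**Conclusion.** The point holds as a criticism of a sample-size input, with moderate confidence. It is not an arithmetic error, since 22 per arm reproduces. The 80% power for a difference of 0.26 is unsupported on the scale of the primary outcome: a single raw word count with SD 0.3 would need about 90% identical scores, and the enlarged sample tolerates an SD only up to 0.383 (0.341 at an assumed 20% dropout). If the SD is 0.5 to 2 words, power for 0.26 words is 57% down to 8%.

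This rests on two things: that the primary score is a single recall count, as the description suggests, and that its SD, or that of its change, is well above 0.38 words. The second is a judgement, not a figure in the article. If 0.26 and 0.3 share some other unit, about 95% power for d = 0.87 stands, but 0.26 must then not be presented as a difference in words.

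**What to change.** 1. Check in the cited study which AVLT-H sub-score the 0.26 ± 0.3 refers to, in what unit, and whether 0.3 is an SD or a standard error. State the answer in Sample size estimates.
2. Unless 0.3 is confirmed as a between-patient SD on the scale of the primary endpoint, withdraw the 80% power claim for 0.26. Replace it with: 35 per arm gives 80% power, at two-sided 0.05, for a between-arm difference of 0.68 SD, or 0.76 SD at 28 per arm if 20% drop out.
3. Name the delayed-recall score that is primary, and convert the detectable difference into words with the blinded pooled SD of that score. Since the ANOVA interaction compares changes, the SD of change in patients with both assessments is the relevant one where it is available.

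The cost is one rewritten paragraph, a look at one source and one blinded SD calculation, which is feasible because the article reports recruitment as ongoing. No extra enrolment is needed. The downside is a less favourable stated detectable effect.

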### Adverse events

As far as we know, no adverse events caused by cognitive training have been reported yet.

### Statistical analysis

To make sure that baseline levels between groups (cognitive training, control) are comparable, questionnaire measures will be analyzed using independent sample t-tests. To determine the training efficacy from baseline to outcome, paired sample t-tests will be used in each group, respectively, for the changes in scores of trained tasks. The neuropsychological changes will be correlated with the score changes of the trained tasks to test the training effect on neuropsychological performance. To determine the training transfer effect, ANOVAs will then be performed on each dependent variable, with time (baseline, outcome) as the within-subjects factor and group (cognitive training, control) as the between-subjects factor.

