Taken together, the present trial will examine the efficacy of cognitive training on episodic memory of aMCI patients. If cognitive training is effective in improving episodic memory function, then greater improvement should be observed in the training group than control group. Moreover, functional and structural data would provide further neural plasticity information about the training-related improvement.

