### Intervention

Cognitive control training will be conducted using a computerized self-adaption training pattern (i.e. individually adjusted task difficulty to bring individuals to their performance maximum). Training tasks which were effectively used in previous studies will be adopted [36], including Flanker task [37], n-back working memory task [38], task switching [39], and Stroop task [40]. To guarantee adaptability to training difficulty, different levels of difficulty will be established as in previous studies with larger sample sizes. Briefly, at the beginning, each individual is assigned a task of similar difficulty. On each training day, the participants are required to complete five tasks three times, with 2 min for each training session (for a total daily test time of 30 min). For each task, the task difficulty will be advanced when the accuracy rate exceeds 80%. To adjust for individual variation in adaptability, the number of types of stimuli, the presentation probability of each type of stimuli, and the size and duration of a stimulus were systematically set. To keep a systematical setting, only one parameter will be adjusted; the remaining parameters will remain unchanged when the task difficulty is elevated. If the accuracy rate of a certain task exceeds 80% of normal counterparts, the task will be substituted for another of higher difficulty. The training program will be implemented five times weekly for 12 consecutive weeks.

In the control group, the training tasks include just the Flanker task and 1-back task. Importantly, a fixed, primary difficulty level will be set. The training tasks will be performed five times weekly, 30 min per session, for 12 consecutive weeks.

With the guidance of doctors, the initial training will be done in clinic and the rest of the training will be completed at home. The training will be supervised by an independent neurologist by telephone and the Internet.

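### For trained-task scores, training efficacy is to be determined by a separate paired t-test in each arm, which cannot separate training from practice; the primary outcome is not affected

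*Protocol article*

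**What the plan says.** The Statistical analysis section sets out the first efficacy step as follows: "To determine the training efficacy from baseline to outcome, paired sample t-tests will be used in each group, respectively". The clause on method, read to its end, is "paired sample t-tests will be used in each group, respectively, for the changes in scores of trained tasks". The arms are compared later in the same section. To assess transfer, an ANOVA is planned on each dependent variable, "with time (baseline, outcome) as the within-subjects factor and group (cognitive training, control) as the between-subjects factor".

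Three other places bear on this:

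- **Background.** If training works, "then greater improvement should be observed in the training group than control group". That is a between-arm standard.
- **Primary outcome measures.** "The primary outcome measure is memory retrieval function assessed by delayed recall of Auditory Verbal Learning Test-Huashan version (AVLT-H"). This is not one of the trained tasks.
- **Intervention.** The training arm works on Flanker, n-back, task switching and Stroop tasks with adaptive difficulty: "For each task, the task difficulty will be advanced when the accuracy rate exceeds 80" per cent. For the comparator, "In the control group, the training tasks include just the Flanker task and 1-back task", at one fixed level. Both arms train five times a week for 12 weeks.

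**The concern.** People who repeat a task many times usually get better at it, whether or not the programme does anything beyond repetition. The control arm is there to measure that gain so that it can be subtracted. A paired t-test in the training arm alone tests whether the mean change is zero, so a pure practice gain counts as evidence of efficacy. Running the same test in the control arm does not repair this: a significant result in one arm and a non-significant result in the other is not a test of the difference between them.

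At stake is any statement that the programme improved performance on the tasks it trains. The Discussion hypothesises that training will enhance cognitive control abilities as well as episodic memory. Trained-task gains are a natural support for the first part, and as planned they would be offered without a controlled comparison.

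**Working it through.** **1. How the trial itself is sized.** The Sample size estimates section uses a between-group difference of 0.26, SD 0.3, two-sided alpha 0.05, power 0.80 and 1:1 allocation. With q1 = q2 = 0.5 its formula becomes total n = 4 × (t for alpha/2 + t for beta)² × 0.3² / 0.26². Iterated with t quantiles this gives 43.8 in total, or 22 per arm, with 80.2% power. The stated 22 therefore reproduces as a per-arm figure for a between-arm comparison. It is raised to 35 per arm to allow for dropout and an unstable SD.

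**2. Exposure to practice.** 5 sessions a week × 12 weeks = 60 sessions in each arm.

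**3. What the paired test does when the arms do not differ.** Let both arms have the same mean gain g, in units of the SD of the change score, and no training effect beyond it. The paired t statistic follows a noncentral t distribution with n − 1 degrees of freedom and noncentrality g√n. With n = 35 the two-sided 5% critical value is 2.032. For g = 0.5 the noncentrality is 0.5 × √35 = 2.96, and the probability of a significant gain is 0.82.

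Because the arms are independent, the pattern of training significant and control not has probability p(1 − p). At g = 0.5 this is 0.82 × 0.18 = 0.15.

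The documents give no practice gain, so g is an assumption and is shown as a range. The row for 22 per arm is included because 35 contains the dropout allowance.

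| n per arm | Result | g = 0.2 | g = 0.3 | g = 0.5 | g = 0.8 |
|---|---|---|---|---|---|
| 35 | Training arm significant | 21% | 41% | 82% | 99.6% |
| 35 | Training significant, control not | 17% | 24% | 15% | 0.4% |
| 22 | Training arm significant | 14% | 27% | 61% | 95% |
| 22 | Training significant, control not | 12% | 20% | 24% | 5% |

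The second pattern cannot exceed 25%, since p(1 − p) peaks at p = 0.5. It falls away at large gains because both arms then become significant.

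**4. What a between-arm test does in the same setting.** With two time points, the time by group interaction is equivalent to a two-sample t-test on change. In 50,000 simulated trials at each of g = 0.3 and 0.5, with 22 and 35 per arm, it rejected 4.8% to 5.2% of the time.

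**5. Which trained tasks allow a between-arm test.** The control arm has no task-switching or Stroop scores, so no comparison is possible there. Flanker is common to both arms. The n-back is common only at the 1-back level. Because difficulty rises in one arm and is fixed in the other, raw scores on these shared tasks are comparable only where the difficulty is the same.

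**The case against.** The strongest reply is that the paired tests are only a check that participants improved on what they practised, and that the real efficacy analysis is the ANOVA. Much of this stands. A reader who stops partway through the sentence might infer that the trial's efficacy, including the primary outcome, is judged within arms. The documents do not support that. The sentence is confined to trained-task scores, delayed recall is not one of them, the ANOVA has group as a factor, and the sample size rests on a between-group difference. The reply does not rescue the sentence itself, which gives the purpose of the paired tests as determining efficacy and not as checking engagement.

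A reader might also infer that a false result here would carry into the transfer or imaging conclusions. Nothing makes the ANOVA depend on a significant paired test. The planned correlation uses the trained-task change scores themselves, not the test result.

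It could be said that the ANOVA on each dependent variable already covers the trained tasks. The section assigns it to transfer, however, and for task switching and Stroop it could not be run.

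Finally, adaptive difficulty complicates the size of the error. If the analysed score is accuracy, rising difficulty would hold it down in the training arm and make a spurious gain less likely; if it is the level reached, this does not apply. The article does not say which is used. An equal standardised gain in both arms is therefore a simplification, and the table illustrates the mechanism without predicting this trial's error rate.

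**Conclusion.** The point holds for the trained-task analysis only. There, the method does not answer the question the sentence sets and conflicts with the between-arm standard in the Background. With 35 per arm and an assumed shared gain of 0.2 to 0.8 SD of change, the training-arm test would show a significant gain in 21% to 99.6% of trials with no difference between arms, against about 5% for a between-arm test in the settings simulated. These figures rest on the assumed gain, on its being equal in both arms, on normally distributed changes and, at 35, on no dropout. The primary comparison and the sample size stand.

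**What to change.** Reword the sentence so that within-arm changes on trained tasks are reported as means with confidence intervals, as a description of performance over training, with no efficacy conclusion drawn from them.

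If efficacy on trained tasks is to be claimed, base it on a between-arm comparison: ANCOVA of the later score on the first-session score, or the time by group interaction. Limit it to Flanker and 1-back, and to scores obtained at a difficulty level common to both arms. The Intervention section says only that individuals start at similar difficulty, so confirm from the software settings that a common level exists. Where there is no comparable score (task switching, Stroop, or levels the control arm never reaches), make no between-arm efficacy claim.

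A short fixed-level block at the last session would supply a clean endpoint, but it is optional. The trial is already recruiting, so it could be collected only from participants who have not yet finished.

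The cost is a change of wording, slightly more analysis work and a more modest claim about trained-task gains. No extra patients are needed.

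### For the trained-task scores only, training efficacy is judged by separate paired t-tests within each arm, which cannot tell adaptive training from practice

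*Protocol article*

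**What the plan says.** The Statistical analysis section of the protocol article plans three follow-up analyses after the baseline comparison.

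- **Trained tasks.** "To determine the training efficacy from baseline to outcome, paired sample t-tests will be used in each group, respectively". The rest of that sentence limits these tests to score changes on the tasks that were trained.
- **Link to neuropsychology.** "The neuropsychological changes will be correlated with the score changes of the trained tasks to test the training effect on neuropsychological performance". As described, this is a correlation of change scores and not a comparison of the arms.
- **Transfer.** "To determine the training transfer effect, ANOVAs will then be performed on each dependent variable". In this model time varies within participants and arm between them, so the interaction of the two is a between-arm comparison of change.

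The Primary outcome measures section names AVLT-H delayed recall, which is not one of the trained tasks. The Background states what effective training would look like for episodic memory: "then greater improvement should be observed in the training group than control group". In the Intervention section both arms train five times a week for 12 weeks. The training arm works at adaptive difficulty. In the control arm "the training tasks include just the Flanker task and 1-back task", at a fixed level.

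**The concern.** A paired t-test within one arm asks whether that arm changed. It does not ask whether it changed more than the other arm. People who repeat a task over many sessions may well improve at it whether or not the difficulty adapts, so a significant gain in the training arm is weak evidence for adaptive training. Setting the two arms' p-values side by side does not help: significance in one arm and not in the other is not a test of their difference.

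The trained tasks are not listed outcomes, but they matter. The Discussion hypothesises a gain in cognitive control abilities as well as in episodic memory, and the trained tasks (Flanker, n-back, task switching, Stroop) measure cognitive control most directly. If the within-arm tests are reported under the label of efficacy, the paper could claim improved cognitive control when the adaptive programme added nothing over the control tasks.

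**Working it through.** **The plan's own figure.** Under Sample size estimates the inputs are δ = 0.26, S = 0.3, two-sided α = 0.05, 80% power and q1 = q2 = 0.5. The printed formula gives (2 + 2) × (1.960 + 0.842)² × 0.09 / 0.0676 = 41.8 in total, or 20.9 per arm. With t quantiles it gives 43.8 in total, or 21.9 per arm. The stated 22 therefore reproduces as a per-arm number. It is sized on a between-arm difference in AVLT-H, which confirms that the primary question is a comparison of arms.

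**Inputs for the trained tasks**
- Sessions: 5 × 12 = 60 in each arm (Intervention).
- n = 35 per arm (Sample size estimates), here with no dropout.
- Two-sided α = 0.05.
- The same standardised paired gain dz in both arms, so no true difference between them. The documents give no practice effect; dz = 0.3, 0.5 and 0.8 is an assumed range.

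**Probability that the paired test in one arm is significant.** With noncentrality λ = dz × √35 and critical value t(0.975; 34) = 2.032,

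P = 1 − F(2.032; 34, λ) + F(−2.032; 34, λ),

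where F is the noncentral t distribution function.

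**Probability that training is significant and control is not.** The arms are independent with the same P, so this is P × (1 − P).

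**Group-by-time contrast.** An independent t-test on change scores, 200,000 simulated trials at each dz.

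| dz | λ | Paired test significant in training arm | Training significant, control not | Group-by-time significant |
|---|---|---|---|---|
| 0.3 | 1.775 | 0.407 | 0.407 × 0.593 = 0.241 | 0.050 |
| 0.5 | 2.958 | 0.820 | 0.820 × 0.180 = 0.148 | 0.050 |
| 0.8 | 4.733 | 0.996 | 0.996 × 0.004 = 0.004 | 0.050 |

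Half of the 5% in the last column, 2.5%, favours training.

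**Sensitivity to dropout.** With only 22 per arm completing, the paired test is significant in 27%, 61% and 95% of trials, and the one-arm-only pattern favouring training occurs in 20%, 24% and 5%. The one-arm-only pattern applies only to tasks scored in both arms.

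**The case against.** A reader who stops before the end of the sentence on paired tests might infer that the trial's whole efficacy conclusion rests on within-arm tests and that the randomised comparison is lost. The documents do not support that. The sentence is limited to trained tasks, and the same paragraph plans a time-by-group ANOVA that covers AVLT-H delayed recall and the MRI outcomes. Nor does the Background contradict the analysis section here: its criterion of greater improvement than control concerns episodic memory, and the ANOVA addresses it.

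Three further objections have weight.

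- *The paired tests may be only a check that participants learned the tasks.* Set against the later transfer analysis, that is a fair reading of the intent. The stated purpose is nevertheless to determine efficacy, so the wording needs to change.
- *The ANOVA on each dependent variable might include the trained tasks.* Possibly, but its sentence is expressly about transfer, so no between-arm test is clearly assigned to them.
- *The size depends on assumptions.* This stands. The section gives no rule that turns a paired p-value into a declaration of efficacy, dz is assumed, and equal gains are a simplification when one arm is adaptive and the other fixed. The training-arm percentages depend only on that arm's own gain; the equal-gain assumption is what makes such a result uninformative about training.

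A reader might also add a multiplicity complaint, because the training arm has more tasks to test than the control arm. That is a separate matter from within-arm against between-arm testing, and the Intervention section mentions five tasks but names four, so it is not relied on here.

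**Conclusion.** The point holds for the trained-task scores and for nothing wider. The stated method for determining training efficacy on those scores cannot separate adaptive training from practice, and no between-arm test is expressly assigned to them. With 35 per arm, an equal practice gain in both arms and assumed dz of 0.3 to 0.8, the training-arm test is significant in 41% to 99.6% of trials in which training adds nothing, where a group-by-time test would be significant in 5%. The misleading one-arm-only pattern occurs in 24% of trials at dz 0.3 and 15% at dz 0.5, and almost never at 0.8. The analysis of AVLT-H delayed recall and the sample size are untouched. The wording should be corrected, but the primary analysis is not at risk from it.

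**What to change.** In the Statistical analysis section:

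1. Report change on the trained tasks within each arm as a mean change with a confidence interval, labelled as a description of learning and not as efficacy.
2. Base any efficacy statement about trained tasks on the between-arm difference in change (group by time) with its confidence interval, limited to tasks scored at the same level in both arms at baseline and outcome. Flanker and 1-back are the candidates, if such scores exist.
3. Make no efficacy statement for a task without such a comparison.

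Items 1 and 3 are changes of wording and need no further patients or data. Item 2 depends on common-level scores. Difficulty rises with accuracy in the training arm and stays fixed in the control arm, so the arms need not share a level by week 12, and the article describes no common-level outcome test of these tasks. If none exists, only descriptive reporting remains. The sponsor also gives up a result on trained tasks that would be easy to make significant.
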